### Patients

#### ***Eligibility criteria***

The eligibility criteria are listed in Table 1. Patients who met the inclusion criteria and none of the exclusion criteria were consecutively enrolled in the trial. Staging of COPD was done according to the GOLD criteria, which is a global initiative and strategy for the diagnosis, management and prevention of COPD [11]. The severity grade was based on historical clinical data obtained through the patient records. Although the severity grade of COPD cannot be determined during an exacerbation, measurements were made prior to randomization to obtain baseline values and to confirm that the patients had a decreased, obstructive lung function in addition to a known diagnosis of COPD.

**Table 1 T1:** Eligibility criteria

**Inclusion criteria**	**Exclusion criteria**
• COPD GOLD stage III-IV (that is, FEV1/FVC <0.70 and FEV1 <50% of predicted value).	• Need of NIV or manual ventilation at time of randomization
• Acute exacerbation of COPD (for example, Anthonisen *et al*. definition [12]).	• Severely overweight^b^
• >45 years	• Serious comorbidity:
• pH >7.35	• Unstable heart disease^c^
• Compliance (see, hear, the ability to understand and carry out self-monitoring tasks).	• Poorly regulated diabetes^d^
• Expected hospitalization > 2 days^a^	• Malignancy
	• Other diseases/conditions that make participation impossible (dementia, delirium etcetera).
	• Temperature >38°C or need for IV antibiotics
	• Noncompliance (nursing home resident, tourist etcetera).
	• Participation in another trial

^a^judged by the attending doctor after initial acute management.

^b^severely overweight, causing immobility or Pickwick Syndrome.

^c^angina pectoris, changes in the electrocardiogram that needed immediate treatment during admission.

^d^need for additional insulin during admission.

*COPD* chronic obstructive pulmonary disease, *GOLD* the global initiative for chronic obstructive lung disease, *FEV1* forced expiratory volume in 1 second, *FVC* forced vital capacity, *NIV* non-invasive ventilation, *IV*, intravenous.

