### Outcomes

#### ***Primary outcome***

The primary outcome was treatment failure defined as:

Readmission due to an exacerbation in the chronic obstructive lung disease within 30 days.

Only readmissions occurring after being discharged from the telemonitoring group or the usual care group was designated a readmission. Patients in both groups were discharged when fulfilling five pre-specified discharge criteria and all telemonitoring equipment was removed from the patient’s home the same day of discharge.

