### Collection of data

All patient data were collected in a case record form (CRF) at baseline, during the intervention, at discharge and again at follow-ups 1, 3 and 6 months after discharge.

Data concerning physiological parameters (pulse, temperature, oxygen saturation, FEV1, and FVC) were collected by a project nurse or project physician or by the ordinary staff at the two hospitals during the ward rounds.

Data concerning readmissions, emergency room visits, rehabilitation, ambulatory visits, deaths, additional prescriptions of prednisone or antibiotics during hospitalization, and length of hospital stays were obtained by searching the hospital databases, The Danish National Patient Registry, and the Danish Civil Registration System, and also by asking the patients at the three follow-up visits. The only data that were solely self-reported from the patient and not obtainable in the hospital databases were the health-related quality of life questionnaires and if there had been any visits to the general practitioner due to COPD. The validated health-related quality of life questionnaires used were: the Saint George Respiratory Questionnaire, (SGRQ), the Clinical COPD questionnaire (CCQ), and the EQ-5D questionnaire, a standardized instrument developed by the Euroqol group.

Also, a user satisfaction questionnaire was handed out to patients in the TT group at discharge and to the nurses who engaged with the ‘outmitted’ patients using the telemedical equipment at the hospital.

The patient user satisfaction questionnaire consisted of 29 questions. Of these, 24 questions were presented in a 5-point Likert-scale (1 strongly disagree through 5 strongly agree) and 5 close-ended questions (yes/no). The questionnaire covers the patient experience in different settings such as the daily ward round, acute calls, the equipment use, and the patient’s general experience of the at home admission with telemedicine technology.

The cognitive status of each patient was evaluated in a substudy using a neuropsychological test battery, including verbal learning, memory capacity and attention and was also evaluated by a self-reported questionnaire: the Subjective Cognitive Functioning (SCF). In the substudy, the patient’s functional status was evaluated by the Instrumental Activity of daily living (IADL)questionnaire.

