### Statistics

All analyses will be done using SAS software version 9.3 http://support.sas.com/software/93. Time to readmission after discharge due to an exacerbation will be assessed using a stratified Cox regression to relax the assumptions of proportional hazards. Differences in readmission rate over time will be assessed using multilevel mixed-effects linear regression analysis with unstructured variance matrix where the baseline values of the outcomes are used as covariates. *P* values below 0.05 will be considered significant for the primary outcome, and *P* values below 0.01 will be considered significant for secondary outcomes. Skewed variables will be power transformed if possible; otherwise, the variables will be transformed into dichotomous responses. Missing values will be replaced using multiple imputations [17]. Survival times will be plotted in a Kaplan-Meier survival curve. Differences between the two groups in prescription of additional antibiotics or steroids due to further exacerbation, need of non-invasive ventilation or mechanical ventilation, emergency room visits, visits to the general practitioner, lung function, bed days, and adverse events will be analyzed with an unpaired Student t-test if data are normally distributed or Mann-Whitney test if not. All categorical data will be analyzed with Chi-square test or Fishers exact test as appropriate. For the health-related quality of life scores, differences from baseline, both within and between study groups, and 95% confidence intervals will be calculated. All analyses will be done on the principle of intention to treat.

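### The baseline-adjusted mixed model is attached to readmission, which has no baseline value, while lung function and quality of life, which have one, get less precise analyses

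*Protocol article*

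**What the plan says.** **Readmission.** The Statistics section of the protocol article names two models. The first is a Cox model: "Time to readmission after discharge due to an exacerbation will be assessed using a stratified Cox regression to relax the assumptions of proportional hazards". The second reads "Differences in readmission rate over time will be assessed using multilevel mixed-effects linear regression analysis with unstructured variance matrix", and continues "where the baseline values of the outcomes are used as covariates". Readmission rate is the only outcome named in that second sentence. The Primary outcome section defines the event as "Readmission due to an exacerbation in the chronic obstructive lung disease within 30 days" and adds "Only readmissions occurring after being discharged from the telemonitoring group or the usual care group was designated a readmission".

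**Lung function.** Under Eligibility criteria, "measurements were made prior to randomization to obtain baseline values". In Statistics, lung function is in the list of outcomes to be compared by an unpaired t-test, or a Mann-Whitney test if not normally distributed.

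**Quality of life (SGRQ, CCQ, EQ-5D).** The plan is: "For the health-related quality of life scores, differences from baseline, both within and between study groups, and 95% confidence intervals will be calculated".

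**Timing.** Collection of data states "All patient data were collected in a case record form (CRF) at baseline, during the intervention, at discharge", and then at the 1-, 3- and 6-month follow-ups.

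**The concern.** The model and the outcome do not match. A linear mixed model with an unstructured covariance matrix and the baseline value as covariate suits continuous outcomes measured before randomization and repeatedly afterwards. The article assigns it to an outcome that is an event or a small count and that cannot have happened at baseline. It does not assign it to the outcomes that fit it.

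Two things are at stake. First, the readmission analysis is not specified in a form that can be followed literally. The article defines no substitute for the missing baseline, such as admissions before the trial, so an analyst would have to improvise. Second, the comparisons of lung function and quality of life give up precision in a trial that, by its own Sample size section, would not reach sufficient power.

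There is also a point of interpretation. Baseline was taken during an acute exacerbation, so improvement within each arm is expected whatever the treatment. Within-arm changes therefore say little about the intervention.

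**Working it through.** The plan gives no figure on this point, so there is none to reproduce. Three checks apply.

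**1. Is there a baseline value for readmission?** Readmissions count only after discharge, so at randomization every patient has the same value, 0. The design matrix with columns [intercept, arm, baseline] for 57 patients (Results section) has 3 columns and rank 2. Coding the baseline as 1 for everyone also gives rank 2. The baseline coefficient is not estimable. The deficiency lies wholly between the baseline column and the intercept, so once that column is dropped the arm coefficient is the plain difference between arms.

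**2. How does a linear model behave on so few events?** Expected 30-day readmissions in both arms together:
- at the 23.1% used for the sample size: 57 × 0.231 = 13.2
- at the 28.5% quoted in the Discussion: 57 × 0.285 = 16.2

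These are sparse data. I enumerated every outcome of a pooled-variance linear comparison at one time point, assuming arms of 28 and 29 (the split is not given) and a nominal two-sided 5% level:

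| Readmission rate in both arms | Type I error, linear model |
|---|---|
| 15% (assumed) | 0.0485 |
| 23.1% | 0.0498 |
| 28.5% | 0.0499 |

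The error rate is held in this simple case. The check does not cover the repeated-measures model.

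**3. What does baseline adjustment gain where a baseline exists?** Let r be the correlation between baseline and follow-up, with equal variances at both times. Relative variances of the between-arm difference (large-sample) are:
- follow-up only: 1
- change score: 2(1 − r)
- baseline-adjusted (ANCOVA): 1 − r²

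So adjusted over change score is (1 − r²) / [2(1 − r)] = (1 + r)/2, and adjusted over follow-up only is 1 − r². The equivalent gain in patients is 57/factor − 57. The documents give no r; the values below are assumed.

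| r | Adjusted ÷ change score | Gain on 57 | Adjusted ÷ follow-up only | Gain on 57 |
|---|---|---|---|---|
| 0.3 | 0.65 | 57/0.65 − 57 ≈ 31 | 0.91 | 57/0.91 − 57 ≈ 6 |
| 0.5 | 0.75 | 57/0.75 − 57 = 19 | 0.75 | 19 |
| 0.7 | 0.85 | 57/0.85 − 57 ≈ 10 | 0.51 | 57/0.51 − 57 ≈ 55 |
| 0.9 | 0.95 | 57/0.95 − 57 = 3 | 0.19 | 57/0.19 − 57 = 243 |

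The change-score columns apply to quality of life. The follow-up-only columns apply to lung function if the t-test compares follow-up values; if it compares changes, the change-score columns apply.

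**The case against.** The best defence is that the sentence is a slip with little consequence. The plural "outcomes" and the unstructured matrix suggest it was written for the repeated continuous measures; that is inference, but plausible. Readmission is covered elsewhere by the Cox model and, as categorical data, by the Chi-square or Fisher test. For lung function and quality of life, the t-test and the change score are unbiased under randomization, and all these outcomes are secondary, judged at P<0.01. Preferring baseline adjustment is then a matter of efficiency, not the correction of an error.

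Much of that stands, and it rules out several stronger readings that a reader might infer:

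- *The model cannot be run.* Not so. The constant column drops out and the arm effect remains estimable.
- *Its standard errors would be invalid.* Not shown. A linear model on a yes/no outcome estimates a risk difference, and at one time point the enumeration above finds the error rate held.
- *Both readmission models fall under the P<0.05 rule.* The text does not say so. It gives that level to the primary outcome, and the rate over time can be read as a supplement. The article also does not say which analysis of 30-day readmission carries the test.
- *Quality of life will be judged on within-arm changes.* Between-arm differences with confidence intervals are planned too, and no within-arm efficacy claim is announced.
- *Baseline adjustment is worth 19 patients.* That holds only at r = 0.5.

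One further limit is fair. The article says physiological parameters were collected on ward rounds, and only the general sentence on patient data mentions the follow-up visits. Measurement of FEV1 and FVC at 1, 3 and 6 months is therefore likely but not stated outright.

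The defence does not supply a baseline value for readmission, nor a reason to leave the measured baselines unused.

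**Conclusion.** The point holds as a misassigned method that should be fixed; it is not a fatal flaw. The article names an outcome and a covariate that cannot go together, and its own definition of readmission shows this without any assumption. The result is a redundant covariate and an unclear analysis, not a biased or impossible one.

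For lung function and quality of life the cost is precision alone. Over assumed correlations from 0.3 to 0.9, the variance after adjustment is 5% to 35% below that of a change score and 9% to 81% below that of a follow-up-only comparison. These figures rest on equal variances at baseline and follow-up, a large-sample formula, complete data on 57 patients, and a correlation that the documents do not give.

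**What to change.** 1. Assign the mixed model (treatment by visit, baseline value and hospital as covariates, unstructured covariance) to SGRQ, CCQ and EQ-5D, and to FEV1 and FVC at the visits where they were measured.
2. Base conclusions on between-arm differences. If within-arm changes from the exacerbation baseline are shown, label them descriptive.
3. Analyse COPD readmissions over 6 months as a count, by negative binomial or Poisson regression with robust standard errors and log time at risk as offset, without a baseline covariate. Label this analysis secondary.
4. Name the one analysis of 30-day readmission that carries the P<0.05 test.

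The cost is rewording of the Statistics section and some SAS code. No new data are needed, provided the lung-function model is limited to visits with measurements.

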**Conclusions:**

The results may have implications on future hospital treatment modalities for patients with severe exacerbations in COPD where telemedicine may be used as an alternative to conventional admission.

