### Sample size

The trial was originally planned to be conducted as a trial of non-inferiority, which determined the method for calculating sample size based on a prior study where the estimated readmission rate was set to be 23.1% [13,14].

The sample size calculation assuming non-inferiority with a predefined margin of 20% or less, with 5% alpha-error and 80% power, showed that a patient number of 70 in each group was needed. The inclusion number was therefore originally set to be 175 patients with an expected drop out of 20%. However, the required sample size was not attainable in the planned study duration and inclusion was stopped as planned after 18 months. This meant that the study would not reach sufficient power, but reporting of the sample size determination will still be done according to the consort statement recommendation [15].

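### The trial is sized against a 20-point non-inferiority margin, but the stated rule for the primary outcome is P<0.05 for a difference; the margin is not used and no replacement hypothesis is stated

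*Protocol article*

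**What the plan says.** Protocol article, Sample size: "The trial was originally planned to be conducted as a trial of non-inferiority, which determined the method for calculating sample size". The inputs are a readmission rate ("the estimated readmission rate was set to be 23.1"%) and a calculation "with a predefined margin of 20% or less, with 5% alpha-error and 80% power". The result is 70 per group, raised to 175 in total for 20% drop-out. The section then says that this number could not be reached in the planned period and that power would be insufficient. It names no hypothesis in place of non-inferiority.

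Protocol article, Statistics: time to readmission is analysed by stratified Cox regression, and differences in readmission rate over time by a mixed model. For the primary outcome, P "values below 0.05 will be considered significant for the primary outcome". The section mentions neither a margin nor a one-sided bound. Confidence intervals are promised only for the quality-of-life scores. All analyses are by intention to treat.

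Protocol article, Results: 57 patients were randomized.

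Protocol article, Abstract, Conclusions: the results may bear on future treatment of severe exacerbations, "where telemedicine may be used as an alternative to conventional admission".

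**The concern.** A non-inferiority design asks whether the data exclude an excess as large as the margin. A difference test asks whether the data exclude equality. The article sizes the trial for the first question and gives a criterion only for the second.

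The mismatch matters more because recruitment fell so far short. In a small trial a difference test seldom rejects, so the most likely outcome is a non-significant P value whatever the truth. Presenting home treatment as an alternative to admission needs evidence that it is not materially worse, and failure to reject equality does not supply that. The outcome is readmission in patients with GOLD stage III-IV disease, so a misread null result could affect care.

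The size of the margin is also hidden. The article writes it as 20% or less, without saying whether this is absolute or relative, and never spells out the readmission rate it would tolerate.

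**Working it through.** **Inputs.** Rate 23.1% in both arms, margin 20%, alpha 5% (sidedness not given), power 80%, drop-out 20% (Sample size); 1:1 allocation (Randomization); 57 randomized (Results); national one-month readmission rate 28.5% (Discussion). The split of the 57 is not given, so 28/29 is assumed, either way round.

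**1. The plan's own figure.** n per group = (z₁₋α + z₁₋β)² × 2p(1−p) / margin².
- Absolute 20 points, one-sided 2.5%: (1.960 + 0.842)² × 2 × 0.231 × 0.769 / 0.20² = 69.7, so 70. Total 140 / 0.80 = 175. Both stated figures reproduce exactly.
- Absolute 20 points, one-sided 5%: 54.9, so 55.
- Relative 20% (0.20 × 0.231 = 0.0462), one-sided 2.5%: about 1,306.

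The margin is therefore 20 absolute points at one-sided 2.5%. It tolerates 23.1 + 20 = 43.1% at home against 23.1% in hospital.

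**2. Margin test with 57 patients, true rates equal.** SE = √[0.231 × 0.769 × (1/28 + 1/29)] = 0.1117.
- Expected 95% CI half-width: 1.96 × 0.1117 = 0.219, or 21.9 points, wider than the margin.
- Power = Φ(0.20/0.1117 − 1.96) = 0.43.
- After 20% drop-out (about 23 per group): SE = 0.1243, power 0.36.
- At a 28.5% rate with 28/29: SE = 0.1196, power 0.39.
- At one-sided 5% instead: about 0.56 with 57 patients, about 0.48 after drop-out. The stated 70 does not match this reading.

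**3. P<0.05 rule when home treatment is truly 20 points worse (43.1% vs 23.1%).** Exact enumeration, probability of a non-significant result:

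| Split (home/control) | Uncorrected chi-square | Fisher |
|---|---|---|
| 28/29 | 62% | 69% |
| 29/28 | 64% | 71% |

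**4. P<0.05 rule when the rates are equal at 23.1%.** Fisher is non-significant about 97% of the time. In about 54% of all trials the result is non-significant by Fisher while the Wald 95% upper limit for the difference still reaches 20 points.

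**5. One possible result.** 12/28 (42.9%) at home against 7/29 (24.1%) is a difference of 18.7 points. Fisher P = 0.17 and chi-square P = 0.13, both non-significant. The Wald 95% CI is 18.7 ± 1.96 × 12.3, or about −5 to +43 points, which reaches more than twice the margin.

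**The case against.** The strongest reply is that much of this is disclosed. The article says "The trial was originally planned to be conducted as a trial of non-inferiority", reports the shortfall and concedes low power. If non-inferiority was given up, a difference test is a legitimate choice. That stands, and it narrows the point: what remains is that the change is never stated and the margin is left without a role.

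A reader might infer that the plan will take a non-significant result as proof that home treatment is as good. The article does not say so. It sets a threshold for significance and no rule for P≥0.05. The aim is worded neutrally as a comparison, the Discussion speaks of possible reductions in readmission, and the abstract's conclusion is hedged. The word superiority is not used either; that the P value tests a difference is inferred from the methods listed. The supportable claim is that a null result could be misread.

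A reader might also infer that even extreme results would escape the rule. That depends on the test: 14/28 against 7/29 gives Fisher P = 0.057 but uncorrected chi-square P = 0.043. The article allows either test for categorical data, so this example proves nothing.

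The probabilities above use two-proportion tests, whereas the first-named analysis is a stratified Cox model. With 30 days of follow-up a similar result is plausible, but it was not calculated.

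Finally, a fuller analysis plan may exist and could hold a margin test. Such an absence would be no finding in a condensed article. Here, though, the article does state a criterion for the primary outcome, and that criterion does not address the hypothesis behind its sample size.

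**Conclusion.** The point holds in this limited form. The sample size rests on excluding a 20-point absolute excess in 30-day readmission. The stated primary criterion tests a difference, the margin is not used, and the current hypothesis is not given.

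With 57 patients the difference test would miss a true excess equal to the margin about 62% to 71% of the time. A proper margin test would itself have only about 43% power, or 36% after 20% drop-out, against the planned 80%. These figures assume a 28/29 split, a 23.1% control rate, one-sided 2.5% for the margin test and two-proportion tests at the two-sided 5% level.

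The documents do not support saying that equivalence will be claimed from a null result, or that the shortfall in power was concealed.

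**What to change.** In the Statistics section:
- State the current primary hypothesis.
- Report the 30-day readmission risk difference, telemedicine minus control, with a two-sided 95% confidence interval in the intention-to-treat set.
- Conclude non-inferiority only if the upper limit is below +20 percentage points; otherwise report the result as inconclusive. Alternatively, state that the margin is abandoned and that no non-inferiority claim will be made.
- State that P≥0.05 is not evidence of non-inferiority.

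In the Sample size section, say that the margin is absolute and tolerates 43.1% against 23.1%. Give the power delivered by 57 patients: about 43% at one-sided 2.5%, about 36% after 20% drop-out.

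A per-protocol analysis is an optional sensitivity analysis; the article defines no such set. The abstract says results were analysed in 2013 while the Statistics section uses the future tense, so if the data have already been unblinded the change should be labelled post hoc.

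The cost is a few sentences, one extra interval and a less favourable stated power. No new data are needed. The change corrects what may be concluded; it does not restore power.

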#### ***Secondary outcomes***

The secondary outcomes were; 1) Prescription of additional antibiotics or steroids due to further exacerbation, 2) need of non-invasive ventilation (NIV) or mechanical ventilation, 3) death from any cause, 4) emergency room visits, 5) visits to the general practitioner, 6) lung function (FEV1, FVC, FEV1% predicted), 7) bed days, 8) health-related quality of life, 9) healthcare costs, 10) applicability, 11) user satisfaction, or 123) adverse events.

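### Lung function is compared by an unpaired two-group test with no baseline term, although baseline was measured before randomization; as a minor point, yes/no outcomes fall under two test rules

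*Protocol article*

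**What the plan says.** The Statistics section of the protocol article puts several secondary outcomes into one sentence. After extra prescriptions of antibiotics or steroids it lists "need of non-invasive ventilation or mechanical ventilation, emergency room visits, visits to the general practitioner, lung function, bed days, and adverse events", and the differences between groups "will be analyzed with an unpaired Student t-test if data are normally distributed or Mann-Whitney test if not". The next sentence adds a rule by data type: "All categorical data will be analyzed with Chi-square test or Fishers exact test as appropriate".

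The lung function outcome is FEV1, FVC and FEV1% predicted (Secondary outcomes). Under Eligibility criteria the article states that "measurements were made prior to randomization to obtain baseline values and to confirm that the patients had a decreased, obstructive lung function". Under Collection of data, the case record form was filled in "at baseline, during the intervention, at discharge and again at follow-ups 1, 3 and 6 months after discharge".

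Baseline enters the Statistics section in two places only. A mixed model with baseline values as covariates is attached to the readmission rate, and differences from baseline are named for the quality-of-life scores. Neither mentions lung function.

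**The concern.** A measurement taken before randomization on the same scale as the outcome is usually the most useful covariate available. For lung function the trial took that measurement and then names a comparison that does not use it. The comparison stays unbiased under randomization; what is lost is precision. That matters here because 57 patients were randomized against 175 planned, and secondary outcomes are judged at 0.01.

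The second, smaller issue is that need of ventilation is naturally a yes/no outcome. It is listed by name for a t-test or Mann-Whitney test and also comes under the categorical rule, so the text gives two tests for one outcome.

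**Working it through.** **The plan's own figures.** The only stated calculation is for the primary outcome. With 23.1% in both arms, a margin of 20 percentage points, two-sided 5% and 80% power: (1.960 + 0.842)² × 2 × 0.231 × 0.769 / 0.20² = 69.7, so 70 per group, and 140 / 0.80 = 175. It reproduces and is untouched by this point. No figure is stated for lung function.

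**Inputs.** 57 randomized (Results), 1:1 allocation (Randomization), taken as 28.5 per arm; alpha 0.01 for secondary outcomes (Statistics). The correlation r between baseline and follow-up lung function is not in the documents; I assume 0.5 to 0.8 and show 0.3 as a low case. Equal variances at the two times are assumed, and the one degree of freedom spent on the covariate is ignored.

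**Formulas.** Relative to a comparison of follow-up values (variance 1), change scores have variance 2(1 − r) and ANCOVA has 1 − r². ANCOVA relative to change scores is (1 − r²) / [2(1 − r)] = (1 + r) / 2. The equivalent number of patients is 57 divided by the relevant ratio.

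| r | Change score, 2(1 − r) | ANCOVA, 1 − r² | Cut vs follow-up values | 57 act like | Cut vs change scores | 57 act like |
|---|---|---|---|---|---|---|
| 0.3 | 1.40 | 0.91 | 9% | 63 | 35% | 88 |
| 0.5 | 1.00 | 0.75 | 25% | 76 | 25% | 76 |
| 0.7 | 0.60 | 0.51 | 49% | 112 | 15% | 67 |
| 0.8 | 0.40 | 0.36 | 64% | 158 | 10% | 63 |

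A weak correlation shrinks the gain over follow-up values but enlarges the gain over change scores. ANCOVA is at least as precise as either for every r in the table.

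**In terms of detectable difference.** At alpha 0.01 and 80% power, follow-up values alone detect (2.576 + 0.842) × √(2/28.5) = 0.905 SD. Multiplying by √(1 − r²) gives 0.864, 0.784, 0.647 and 0.543 SD for r = 0.3, 0.5, 0.7 and 0.8. Power for a 0.5 SD difference is 24.6% without baseline, and 27.5%, 34.6%, 52.7% and 71.6% with it.

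**Yes/no outcomes.** With an assumed 29/28 split and a true event rate of 20% in both arms, the type I error at nominal 0.01 is 0.0089 for the t-test, Mann-Whitney and uncorrected chi-square alike, and 0.0060 for Fisher. For invented sparse counts of 0/29 against 6/28, the p-values are 0.0078 (t), 0.0090 (Mann-Whitney), 0.0084 (chi-square) and 0.0104 (Fisher). The choice can cross 0.01, but only by a narrow margin.

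**The case against.** The strongest reply on lung function is that the article never says raw follow-up values are compared. An unpaired t-test on change from baseline would fit the sentence. The clause on baseline covariates may also be condensed wording meant for repeated measures in general, since readmission after discharge has no obvious baseline value. Both readings are possible. As written, however, the covariate clause belongs to the readmission rate, change from baseline is named only for quality of life, and change scores would still be less precise than ANCOVA. A reader might infer that the baseline values are certainly thrown away; the text supports only that no baseline term is specified.

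A reader might also take the gain to be a near doubling of the sample. That is the r = 0.7 case against follow-up values alone. Baseline was measured in an acute exacerbation, and the article itself says severity cannot be graded at that time, so r may be low. Collection of FEV1 after discharge rests on the general sentence about the case record form; the sentence on physiological parameters speaks of ward rounds. Drop-out would reduce the 57, though not the percentage cuts.

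On the tests, it is tempting to say that the whole list contradicts the categorical rule. It does not: lung function, bed days and visit counts are not categorical, and the categorical sentence can fairly be read as letting data type decide. Nor does the text show that visits and adverse events need a count model. Mann-Whitney is valid for counts, a further rule says "Skewed variables will be power transformed if possible; otherwise, the variables will be transformed into dichotomous responses", general practitioner visits may have been recorded only as any or none, and neither an excess of zeros nor unequal time at risk is documented. Negative binomial regression would be a preference. Which effect estimates accompany each test can be left to a full analysis plan.

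**Conclusion.** The point holds for lung function: the named comparison has no baseline term although a pre-randomization value exists. Adding it cuts the variance of the arm difference by 25% to 64% against follow-up values, or by 10% to 25% if change scores were meant, for an assumed r of 0.5 to 0.8; at r = 0.3 the cut against follow-up values is 9%. This is lost precision, not bias. The overlap of two test rules is real only for yes/no outcomes such as need of ventilation, and its numerical effect is small. All outcomes concerned are secondary, and the primary analysis is unaffected.

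**What to change.** Take lung function out of the t-test/Mann-Whitney sentence. State that FEV1, FVC and FEV1% predicted are compared at each visit by ANCOVA, or jointly over visits by a mixed model, with the pre-randomization value of the same measure as covariate, and report the adjusted difference with its confidence interval.

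Take need of ventilation, and any other outcome recorded as yes/no, out of the same sentence so that only the chi-square/Fisher rule applies to them.

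The cost is a change of wording. The baseline values were collected, and no new data or patients are needed.
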